**Methods/design:**

We are conducting a randomized, double-blind, placebo-controlled trial of oxytocin-enhanced motivational interviewing group therapy (MIGT). Oxytocin or placebo 40 IU is administered intranasally in conjunction with six, weekly MIGT sessions. We will recruit 50 MSM, initiating treatment for MUD from specialized community health programs in San Francisco, CA, USA. Individuals will be randomized (1:1) to receive six, weekly sessions of MIGT with or without oxytocin. Our primary outcome is session attendance. Other outcomes of interest include: measures of group cohesion, anxiety, psychophysiology, and stimulant craving and use.

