### Power analysis

A sample size of 25 per treatment condition will provide us with > 99% power to detect an effect size comparable to the large between-condition effect size (*d* = 1.44) observed for attendance from our preliminary 3-week trial in cocaine users [53] with a two-tailed alpha = 0.05. In addition, this sample size will provide 80% power to detect an effect size of 0.81 or greater.

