### Data Analysis Plan

Descriptive statistics will be used for demographic information and other baseline characteristics. Our dichotomous primary outcome measure (in attendance/absent) will be compared between oxytocin and placebo treatment conditions using generalized estimating equations to accommodate for correlations among the observations originating from the same participant and correct for interdependence resulting from MIGT cohort membership. Secondary outcomes collected at each MIGT session consist of group cohesion as measured by the GQ, self-reported anxiety as measured by the STAI-6, psychophysiological measures (including heart rate, HF-HRV, and temperature), methamphetamine craving as measured by the MCQ-Br, and urine drug screen. Given the exploratory nature of this novel study design, we will use descriptive statistics and estimate Cohen’s *d* effect sizes for secondary outcomes. Effect sizes will be calculated by subtracting the mean change in the oxytocin group from the mean change in the placebo group and dividing by the pooled baseline standard deviation. If there is substantial missing data, we also will consider using mixed linear models or multiple-imputation techniques to estimate mean change values in each treatment group with greater accuracy. Additional exploratory outcome measures collected at two timepoints, baseline and after the final MIGT session, consist of the SRTB, SPS, IOS, and RTCQ and will be processed using the same methodology. Results of secondary outcomes will be considered exploratory, and further confirmatory studies would be needed to confirm the results. ECR-S, ACE, STAI, and subsections of the ASI-Lite, along with baseline measurements of the SPS, IOS, SRTB, and RTCQ, will be explored as potential predictors of oxytocin response using Pearson’s correlation coefficients.

In addition to utilizing psychophysiology measures recorded during MIGT sessions as a secondary outcome variable in our main data analysis approach, we will utilize models designed to explore physiological synchrony, contagion, and other aspects of shared physiological states [84].

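### Pearson correlations with no stated placebo contrast measure prognosis and do not by themselves show who responds to oxytocin

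*Protocol article*

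**What the plan says.** The Data Analysis Plan names the candidate variables as "ECR-S, ACE, STAI, and subsections of the ASI-Lite, along with baseline measurements of the SPS, IOS, SRTB, and RTCQ". It says that they "will be explored as potential predictors of oxytocin response using" Pearson correlations. The sentence fixes a target (response to oxytocin) and a method (Pearson r). It does not say:

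- which outcome stands for response;
- whether the oxytocin arm, the placebo arm or both enter the correlation;
- whether any threshold will be used;
- how, if at all, the arms will be contrasted.

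The same section does contrast the arms elsewhere. Attendance is compared by generalized estimating equations (GEE) that allow for repeated observations and cohort membership. Secondary outcomes are summarised as the between-arm difference in mean change divided by the pooled baseline SD. SPS, IOS, SRTB and RTCQ, which are on the predictor list, are also exploratory outcomes handled as change.

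Under Self-assessment measures, the Adverse Childhood Experiences score is justified partly by earlier evidence that it alters the effect of oxytocin on cortisol reactivity. That is a statement about effect modification.

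**The concern.** A man's response to oxytocin is his outcome on the drug compared with what it would have been on placebo. A baseline variable predicts that response only if the oxytocin-minus-placebo difference changes with the variable. A variable that goes with better attendance or less craving whatever the man receives is prognostic, and it will correlate with outcome in the oxytocin arm and in the pooled sample even if oxytocin does nothing.

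Readiness to change and attachment style could plausibly be such variables. A correlation reported under the heading of oxytocin response could then be read as evidence about whom to treat. The article says that the trial is meant to inform later trials, so the label matters even for exploratory work. The placebo arm needed for the right comparison is already in the design.

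**Working it through.** **The plan's own figures.** The only power statement (Power analysis: 25 per arm, two-sided 0.05) concerns attendance. The noncentral t gives 99.9% at d = 1.44 and 80.1% at d = 0.81, so both stated figures reproduce. Neither bears on the predictor analysis, for which the article gives no figure.

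**Inputs.** From the article: 25 men per arm, 1:1 allocation, cohorts of four to six, one study drug per cohort. Assumed here because the article gives none: the correlation r, a flag at p < 0.05, the arm analysed, normally distributed scores and outcomes, and independent men.

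**Step 1: a prognostic score with no differential response, oxytocin arm only.** By Fisher's z with n = 25, the probability of flagging is about Φ(atanh(r) × √22 − 1.96), with √22 = 4.690.

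| r in both arms | atanh(r) × 4.690 | minus 1.96 | flagged |
|---|---|---|---|
| 0.4 | 1.987 | 0.027 | 51% |
| 0.5 | 2.576 | 0.616 | 73% |
| 0.6 | 3.251 | 1.291 | 90% |

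**Step 2: simulation of the same question.** There were 20,000 trials per row, 25 per arm, and the same correlation in both arms.

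| r in both arms | oxytocin-arm r | pooled r | significant on oxytocin, not on placebo | interaction test |
|---|---|---|---|---|
| 0.3 | 32% | 57% | 22% | 5% |
| 0.4 | 52% | 83% | 25% | 5% |
| 0.5 | 75% | 97% | 19% | 5% |

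The first column agrees with Step 1 to within 2 points. Pooling flags prognostic scores more often because it uses 50 men. An informal reading of two p-values side by side still mislabels the score in 19 to 25% of trials. Only the formal contrast holds its nominal level.

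**Step 3: the reverse error.** With r = +0.5 on oxytocin and −0.5 on placebo, a true modifier, the pooled correlation detects it in 8% of trials and the interaction in 96%.

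**Step 4: what the right analysis can deliver.** With r = 0.5 on oxytocin and 0 on placebo, simulated interaction power is 42%. With 0.4 and 0 it is 29%. As a check, Fisher's comparison of two correlations has SE √(1/22 + 1/22) = 0.3015:

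- 0.5 versus 0: 0.549 / 0.3015 = 1.822, and Φ(1.822 − 1.96) = 45%.
- 0.4 versus 0: 0.424 / 0.3015 = 1.405, and Φ(1.405 − 1.96) = 29%.

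**Step 5: number of cohorts.** 50 / 6 = 8.3 and 50 / 4 = 12.5, so about 8 to 13 cohorts in all. Steps 1 to 4 ignore this clustering.

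**Step 6: coupling, only if such pairs are run.** If a baseline is correlated with its own change, and the two time points have equal variance and test-retest correlation ρ, the expected correlation without any drug effect is −√((1 − ρ)/2). This is −√0.20 = −0.45 at ρ = 0.6 and −√0.10 = −0.32 at ρ = 0.8. Both values of ρ are assumed.

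**The case against.** The strongest reply is that this is one sentence in a condensed article. It speaks of exploration and of potential predictors, and the choice of outcome, arm and contrast may sit in a fuller document. The section also describes the design as exploratory and says that secondary results need confirmation. Much of this stands, and it rules out several stronger readings:

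- **That Pearson correlations can never answer the question.** Coefficients from each arm can be compared formally. The fair statement is that no such comparison is stated and that a correlation alone does not supply it.
- **That the plan has a 73% false-positive rate.** That figure needs r = 0.5, the oxytocin arm alone and a p < 0.05 rule. The article's only alpha belongs to the attendance power statement.
- **That the correlations will be distorted by coupling.** The article never says that baseline SPS, IOS, SRTB or RTCQ will be set against its own change. For attendance, the primary outcome, no such coupling arises.
- **That cohort membership will be ignored.** The predictor sentence mentions no adjustment, but Limitations and future directions says that the complications of group therapy will be taken into account.
- **That patient selection in later trials will be misdirected.** No decision or enrichment rule depends on this analysis.

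The exploratory label does not answer the core point. It excuses imprecision and multiplicity, but not estimating a different quantity from the one named. Nor is the method simply left open, because the article names it together with its purpose. Low interaction power is a real limit, but it is a reason for cautious reporting and not for replacing the contrast with a prognostic correlation.

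**Conclusion.** The point holds in a limited form. As written, the analysis estimates how baseline scores relate to outcome and labels the result as response to oxytocin, with no stated placebo contrast. If correlations in the oxytocin arm were screened at p < 0.05, a score with no differential effect would be flagged in roughly half to nine-tenths of trials for r between 0.4 and 0.6, against about 5% for an interaction test. These percentages illustrate the gap between the two questions under assumed correlations, normal outcomes and independent men. They are not error rates of the stated plan. Coupling is a conditional warning only.

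The primary comparison of attendance does not depend on this analysis. Severity is modest, but the wording should be corrected before any correlation is reported as a predictor of drug response.

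**What to change.** Replace the Pearson correlations with an arm-by-baseline interaction in a model suited to each outcome. For attendance this can be the GEE already planned. A formal between-arm comparison of the correlations is an acceptable alternative, although correlations also depend on the spread of scores in each arm, so slopes are easier to interpret.

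The analysis should allow for cohort membership with a method suited to about 8 to 13 cohorts. Report the interaction estimate with its confidence interval and the slope in each arm, and label the result hypothesis-generating. If the sponsor prefers to keep simple correlations, call the variables prognostic correlates and drop the reference to oxytocin response.

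Where the predictor is the outcome's own baseline, do not interpret a raw baseline-change correlation. With baseline, arm and their interaction in a linear model, the interaction coefficient is the same for final value and for change; only the displayed slopes differ.

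The cost is a change of wording and a few model terms, with no new data. The downside is imprecision: power is only about 42% even for r = 0.5 on oxytocin against 0 on placebo, and clustering would be expected to lower it further.

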## Discussion

The high prevalence of MUD among MSM leads to significant health disparities, including increased risk for HIV seroconversion. Currently, no psychopharmacological agent is FDA-approved for the treatment of MUD. This investigation represents the first randomized clinical trial to administer the social peptide, oxytocin, to individuals with MUD. Data from this study should inform further development of oxytocin’s role in psychopharmacological-psychosocial combination treatment. Outcomes aim to further elucidate the potential mechanisms of OE-MIGT for MUD. Overall, this study aims to address methamphetamine use, treatment engagement, and stress reactivity in a difficult-to-treat population for whom current attrition rates are high (Additional file 1).

### Limitations and future directions

The current study will only include men who identify as having sex with men; therefore, results may not generalize to other genders and sexual orientations. There may be further selection bias regarding the motivation and engagement of participants who choose to take part in our study protocol. Furthermore, studies with substance use disorder populations often must deal with missing data from attrition. Our self-report measures increase the risk of reporting bias, although objective measures of psychophysiology will also be examined. Lastly, group therapy studies present inherent complications regarding statistical analyses. We will take these factors into account, although likely at the expense of statistical power. Despite these limitations, this study has many novel features and effect sizes will contribute to ongoing research. Future goals involve the further development of oxytocin-enhanced psychotherapy and expanding this treatment modality to other patient populations.

## Trial status

Protocol version 1.0. Recruitment started on 27 March 2017 and is estimated to end around 31 December 2018.

## Abbreviations

ACE: Adverse Childhood Experiences
AIDS: Acquired immune deficiency syndrome
ANOVA: Analysis of variance
ASI-Lite: Addiction Severity Index-Lite
CLIA: Clinical Laboratory Improvement Amendments
DFA-1: Detrended Fluctuation Analysis
ECR-S: Experiences in Close Relationships-Short
GQ: Group Questionnaire
HF-HRV: High-frequency heart rate variability
HIV: Human immunodeficiency virus
HRV: Heart rate variability
IOS: Inclusion of Others in the Self
MCQ-Br: Meth Craving Questionnaire-Brief
MI: Motivational interviewing
MIGT: Motivational interviewing group therapy
MINI: Mini International Neuropsychiatric Interview
MITI: Motivational Interviewing Treatment Integrity
MSM: Men who have sex with men
MUD: Methamphetamine use disorder
OE-MIGT: Oxytocin-enhanced motivational interviewing group therapy
OTSE: Oxytocin Side Effect Checklist
RTCQ: Readiness to Change Questionnaire
SCID-5: Structured Clinical Interview for DSM-5
SPS: Social Provisions Scale
SRTB: Sexual Risk-Taking Behavior questionnaire
STAI: State-Trait Anxiety Inventory
STAI-6: Six-item State-Trait Anxiety Inventory
TLFB: Timeline Follow Back
US: United States
